## Abstract

**Background and aim:**

Rehabilitation programs have been shown to have a positive impact on patients' health and work ability. However, the durability of these effects and the extent to which patients alter their health behaviors remain underexplored. This study is divided into two parts; the first assesses the effectivity of rehabilitation programs for orthopedic patients and the durability of effects. The second part examines psychological determinants of aftercare health behaviors.

**Subject and methods:**

Study Part 1 employs a longitudinal study design with up to nine measurement occasions encompassing a three-year follow-up period. Treatment is provided as per orthopedic indications through rehabilitation centers. Measures include subjective health, work ability, body weight, and physical activity behavior. Study Part 2 incorporates a mixed-methods design, involving both quantitative and qualitative assessments. The quantitative component aims to recruit a subsample from Study Part 1 to assess psychological determinants of aftercare health behaviors over 12 to 24 weeks using Ambulatory Assessment. The qualitative component aims to explore the reasons for maintenance and discontinuation of health behaviors and involves a reflexive thematic analysis of interviews with at least 16 individuals, analyzing the differences between those who adopt and those who discontinue their aftercare health behavior.

**Discussion:**

This comprehensive research project may offer insights into the long-term effectivity of rehabilitation programs. Furthermore, it may foster a more profound understanding of the successful incorporation of health-promoting aftercare behaviors, such as physical activity, into everyday life. Therefore, this study may contribute significantly to the evolving field of patient-centered rehabilitation.

**Trial registration:**

The trial has been registered at the German Register of Clinical Studies (DRKS) with the registration number: DRKS00032257

## Background

1

Rehabilitation services are a vital and integral component of the German health care system, especially in the context of orthopedic impairments. These services not only constitute a significant financial investment within the system (1, 2) but also play a crucial role in enabling individuals with health impairments to return to work and regain quality of life. On the one hand, patients are supported in their healing process by health professionals, aiming to enhance their overall health and work ability as they progress through the program. On the other hand, patients are educated and guided to adopt health-promoting behaviors, such as regular physical activity, to promote long-term health. This dual focus ensures that patients not only recover but also acquire the necessary skills and understanding to maintain their health in the long-term, reducing the likelihood of requiring further rehabilitation services. By targeting these areas, rehabilitation programs are designed to provide comprehensive care that addresses both the immediate needs and future well-being of patients with orthopedic impairments.

Studies on cardiovascular (3), oncological (4), neurological (5) and musculoskeletal (6, 7) rehabilitation interventions showed positive effects on previously impaired health parameters. In addition, a reduced mortality rate was observed (3, 8). A recent meta-analysis yielded that orthopedic rehabilitation programs in Germany increase patients' quality of life and work ability (9). However, the existing research on the effectiveness of rehabilitation programs reveals some critical gaps and shortcomings that warrant further investigation. Most notably, a control group is an essential component for robustly evaluating the effectivity of the intervention which is missing in many studies. Moreover, the durability of these positive effects remains largely unclear, with few studies incorporating a follow-up period exceeding 12 months (9). This research gap regarding long-term durability underscores the need for more comprehensive research to optimize the effectivity of rehabilitation programs.

Physical activity is a critical aspect of rehabilitation, particularly for maintaining benefits after rehabilitation. In addition, it reduces the likelihood of overweight and obesity (10–12). However, understanding the underlying psychological processes that influence the adoption and maintenance of aftercare health behaviors such as physical activity is complex. Dual process approaches suggest that two processes, one that is automatic and implicit and another that is reflective and explicit, influence health behavior (13, 14). For example, in the Physical Activity Adoption and Maintenance Model [PAAM, (14)], the variables affect and habit are rather described as implicit processes, while intention is rather understood as a construct of explicit processes. The theory postulates that these variables are influenced on the one hand by the experience during physical activity and on the other hand also influence future activity behavior. Current research indicates that especially intention (15), perceived behavioral control (16), anticipated affect (17), remembered affect (18), habit (19) and intrinsic motivation (20) may explain health behavior.

### Objectives of the study

1.1

WiN-Reha (“Wirksamkeit und Nachhaltigkeit von Rehabilitationsmaßnahmen und die Analyse von Determinanten des Gesundheitsverhaltens”) is the acronym for the project and comprises two study parts, each with specific objectives aimed at contributing to the development of rehabilitation programs for orthopedic impairments. The study takes a comprehensive approach by employing both longitudinal and mixed-methods designs to investigate various aspects of rehabilitation.

#### Study Part 1: effectiveness and durability of effects of orthopedic rehabilitation programs

1.1.1

The primary objective of Study Part 1 is to evaluate the effectiveness of rehabilitation programs for patients with orthopedic impairments. The focus extends beyond the immediate outcomes, aiming to investigate the durability of effects. The criteria for evaluating the effectiveness and durability are: (i) subjective physical and mental health, (ii) work ability, (iii) body weight, and (iv) physical activity. Subjective health and work ability are crucial indicators to return to work which is the main aim of rehabilitation providers. Close correlates of these indicators and a healthy lifestyle are participants' body weight and the amount of regular physical activity in everyday life.

#### Study Part 2: study of psychological determinants of aftercare health behaviors

1.1.2

Study Part 2 adopts a mixed-methods design consisting of quantitative and qualitative methods. The objective of the quantitative component is to analyze the influence of specific psychological determinants on aftercare health behaviors. This includes examining how intention, anticipated affect, experienced affect, habit, and motivation influence the adoption and maintenance of aftercare health behaviors. The qualitative study aims to analyze the conditions that affect success or failure in completing an aftercare health behavior. By exploring patients' experiences and challenges, this part of the study seeks to gain knowledge about why patients either follow through with their aftercare health behavior or drop out.

## Methods

2

The methods of Study Part 1 and Study Part 2 will be explained in separate sections.

### Methods of Study Part 1

2.1

#### Sampling and participants

2.1.1

Eligibility criteria for participating in the study are that patients need to be at least 18 years old, have basic knowledge of the German language, and the reason for their rehabilitation is an orthopedic impairment prescribed by the German pension fund. There are no further inclusion criteria regarding the type of orthopedic impairment. Participants will be recruited at two different measurement occasions, one before the rehabilitation program starts and one during the first few days of the rehabilitation program. For the first measurement occasion, patients receive information about the study and the first questionnaire via post several weeks before the rehabilitation program starts (t_0_). Rehabilitation centers send out the study material together with the usual information material regarding the rehabilitation program itself. Patients that did not participate in the study at the first measurement occasion can still be recruited at the second measurement occasion (t_1_) which is taking place at the beginning of the rehabilitation program in the rehabilitation centers. Participants that already participated in the first measurement occasion (before rehabilitation started) also fill out the second questionnaire at the beginning of the rehabilitation program (t_1_). This procedure allows for a comparison of the indicators' development from the time without a rehabilitation program with the indicators' development after the rehabilitation program has started. Participants will be informed of the purpose of the study and will give their written consent to participate voluntarily. Currently, five rehabilitation centers in Germany are part of the study. The patients will receive a 50€ voucher, if they fill out the questionnaires at all measurement occasions. Participants are reminded by the research team via e-Mail or phone to fill out the questionnaires to increase participation in the study.

A power analysis was conducted with a small effect size as the evidence regarding the efficacy of rehabilitation programs is insufficient. A meta-analysis about the effects of cardio-vascular rehabilitation on health-related quality of life yielded effect sizes of 0.17–0.25 (21). Due to a large heterogeneity in this meta-analysis and because cardio-vascular rehabilitation programs are different from orthopedic rehabilitation programs, a standard mean effect size of 0.10 was chosen. The power analysis with Cohens *f* = 0.05, *α *= 0.05, 1-*β* = 0.80, a correlation among repeated measures of *r* = 0.50 and a design with eight measurement occasions since the start of rehabilitation program using an analysis of variance (ANOVA) with repeated measurements (within-between interaction) resulted in *n* = 360 participants. Considering a dropout after each measurement occasion of 15%, the recruitment of *n* = 1,101 participants is planned.

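### Study Part 1: the recruitment target of 1,101 multiplies 360 by 1.15 eight times instead of dividing by 0.85 per loss, so it does not leave 360 complete cases; the shortfall depends on an unstated entry split

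*Protocol article*

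**What the plan says.** The sample size for Study Part 1 is in section 2.1.1 (Sampling and participants) of the protocol article. The inputs are "The power analysis with Cohens *f* = 0.05", a two-sided-equivalent α of 0.05, "1-*β* = 0.80, a correlation among repeated measures of *r* = 0.50", and "a design with eight measurement occasions since the start of rehabilitation program". The test is a repeated-measures ANOVA for the within-between interaction, and the result is 360 participants.

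The attrition step follows at once: "Considering a dropout after each measurement occasion of 15%, the recruitment of" leads to the statement that "1,101 participants is planned". The article gives neither the inflation formula nor the number of losses applied.

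Two other places bear on that number. Section 2.1.1 recruits first by post before rehabilitation (t0) and allows those who did not join then to enter at the start of rehabilitation (t1). Section 2.1.3 (Data collection) gives nine occasions (t0 to t8) for the first route and eight (t1 to t8) for the second. The split between the routes is not stated.

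**The concern.** The two stated numbers and the stated dropout rate do not fit together. 1,101 is exactly what results from adding 15% to 360 eight times. Adding 15% does not undo a loss of 15%: 1.15 × 0.85 = 0.9775, so each step falls 2.25% short and the error compounds.

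A reader of section 2.1.1 will take it that 1,101 recruits secure 360 complete cases and 80% power at three years. If they do not, the power claim for the durability question is somewhat too favourable. The sponsor also cannot tell by how much, because the number of losses is not written down.

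**Working it through.** **1. Reproduce 360.** Noncentral F for the within-between interaction, with λ = f² × N × m/(1 − r), df1 = (g − 1)(m − 1) and df2 = (N − g)(m − 1). From section 2.1.1: f = 0.05, m = 8, r = 0.50, α = 0.05. The number of groups g is not stated; g = 2 is assumed because it reproduces the plan's figure.

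- N = 360: λ = 0.0025 × 360 × 8/0.5 = 14.4, df1 = 7, df2 = 358 × 7 = 2,506, power 80.03%.
- N = 359: power 79.90%.

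So 360 is the smallest N that reaches 80%. Three groups would give 461.

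**2. Reproduce 1,101.**

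| k | 360 × 1.15^k | 360/0.85^k, rounded up |
|---|---|---|
| 6 | 832.7 | 955 |
| 7 | 957.6 | 1,123 |
| 8 | 1,101.2 | 1,322 |

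Only 360 × 1.15^8 gives 1,101. No division by 0.85 does.

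**3. Cross-check in Study Part 2.** Section 2.2.1 inflates 72 to 226 for a 10% loss each week over 12 weeks. 72 × 1.10^12 = 225.97, the same multiplication. Division gives 72/0.90^12 = 254.9 (255) for twelve losses, or 72/0.90^11 = 229.4 (230) for eleven. Two exact matches make coincidence unlikely.

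**4. Count the losses.** For t1 entrants, seven losses precede t8; a loss after t8 removes no data. For t0 entrants, eight losses precede t8.

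**5. Expected complete cases from 1,101.** With a share p entering at t0, completers = 1,101 × [p × 0.85^8 + (1 − p) × 0.85^7], where 0.85^7 = 0.3206 and 0.85^8 = 0.2725. Power is from step 1 at that number of completers. The values of p are illustrative.

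| Share entering at t0 | Completers | Complete-case power | Recruits needed for 360 |
|---|---|---|---|
| 0% (k = 7) | 353.0 | 79.1% | 1,123 |
| 10% | 347.7 | 78.3% | 1,141 |
| 20% | 342.4 | 77.6% | 1,158 |
| 50% | 326.5 | 75.2% | 1,215 |
| 100% (k = 8) | 300.0 | 70.8% | 1,322 |

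The last row also covers t1 entry if eight losses are counted. The target misses 360 in every row: by 7 completers at best and 60 at worst.

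**The case against.** The strongest reply is that the error nearly cancels on the design that was powered. The power analysis names the eight occasions from the start of rehabilitation, so only seven losses count. The wrong multiplier and one step too many then offset each other: 1,101 against 1,123 is 22 recruits, or 2%, and power is 79.1%. Against a 15% dropout rate that is itself a planning guess, that is immaterial. This stands for the case where everyone enters at t1.

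It does not cover the design as described. Recruitment starts at t0, t1 is the second chance, and the Discussion wants pre-rehabilitation recruits to form the control group. Some of the 1,101 are therefore expected to face eight losses.

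The other side also rightly limits the harm. A reader might infer that power is really 71%. The documents do not support that as the expected value. It requires every participant to enter at t0, or the exponent of a rejected formula to be carried into the correct one. Section 2.1.1 provides for t1 entry, and the Discussion names recruitment before rehabilitation as a possible challenge.

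Finally, the powers above are for complete cases. Section 2.1.4 (Data analysis) foresees multiple imputation or full-information maximum likelihood if necessary, and adds latent growth curve models. Partial completers could then contribute, so these figures may be pessimistic. However, the sample-size paragraph takes no credit for this: it inflates to 360 for a repeated-measures ANOVA.

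**Conclusion.** The inflation step is wrong as written, and this is established by exact reproduction in both study parts. Under the stated 15% loss, 1,101 recruits do not leave 360 complete cases for either possible count of losses.

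The size of the shortfall is not established. It runs from 353 completers and 79.1% power (all enter at t1) to a lower bound of 300 and 70.8% (all enter at t0, or eight losses). Where the trial falls between these depends on the t0 share, which the article does not give. The power values rest on two groups and on complete-case analysis.

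A reader might also infer that the whole sample-size calculation has failed. It has not: 360 reproduces under the two-group assumption, and only the step from 360 to 1,101 is at fault. The point is of moderate weight. It calls for a corrected statement, and does not show that the study is materially underpowered.

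**What to change.** In section 2.1.1, replace the inflation with 360/(1 − 0.15)^k. State k and the occasion (t0 or t1) at which the 1,101 are counted, and give the expected share entering at t0. State the number of groups assumed in the power analysis.

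Keep 1,101 as the recruitment figure, and restate what it is expected to deliver: about 353 complete cases and 79% complete-case power for t1 entry, falling to 300 and 71% as the lower bound. If the sponsor relies on imputation or full-information maximum likelihood to offset the loss, say so there.

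In section 2.2.1, correct the same slip behind 226: division gives 230 for eleven losses or 255 for twelve, so state which applies.

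The Part 1 cost is a sentence or two and a slightly less favourable power statement. No extra participants are needed if the figures are restated and the target is not raised. For Part 2, the sponsor can likewise restate the expected completers from 226: 226 × 0.90^11 = 70.9 or 226 × 0.90^12 = 63.8.

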#### Rehabilitation programs

2.1.2

Orthopedic rehabilitations programs in Germany are offered stationary or as an outpatient program in rehabilitation centers. Typically, rehabilitation programs last three to four weeks and comprise different services such as physiotherapy, medical training therapy, and health education. For some indications, standards for treatments exist based on scientific evidence such as for knee and hip joints, but this is not the case for all orthopedic indications (22). Therefore, the content and structure of rehabilitation programs can vary between rehabilitation centers. Rehabilitation programs at the participating rehabilitation centers will be executed as usual and the impact of the study will be limited to the data collection. Therefore, this treatment is not an intervention provided by the research team, but rather treatment as usual.

#### Data collection

2.1.3

Data collection started in September 2023 and baseline measurements will be completed approximately in January 2025. The study design consists of nine measurement occasions for participants that are recruited in the time before the rehabilitation program starts (t_0_–t_8_). For participants that are recruited at the beginning of the rehabilitation program in the rehabilitation center, the study comprises eight measurement occasions (t_1_–t_8_). Pre (t_1_) and post (t_2_) measurements are conducted at the beginning and at the end of the rehabilitation program to assess the effectivity. Based on their preference, the participants are contacted by e-mail or mail for the further measurement occasions (t_2_–t_8_). The interval between the measurement occasions after the rehabilitation is completed (t_2_–t_8_) is six months, resulting in a total follow-up period of three years. The study design for Study Part 1 is provided in Figure 1.

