##### Physical activity

2.1.3.4

The items of the Patient-Centered Assessment and Counselling for Exercise Plus Nutrition (PACE+), which were originally developed for adolescents (31), are used to assess physical activity in everyday life. The items were translated into German (32) and successfully used in comprehensive long-term studies not only with children and adolescents, but also with adults (33, 34). Two items record how many days per week participants were active for at least 60 min at moderate intensity. The first item refers to the last week and the second to a normal week. The response scale ranges from 0 to 7 days. Before answering these questions, physical activity is defined as any activity that makes the heart beat faster and increases breathing for some time. Examples such as walking to work, running, dancing, and swimming are given. The average of the two items builds the final physical activity score. The items showed interclass correlation coefficients between 0.64 and 0.79, which can be considered good. Validity can also be rated as good, as data from the PACE + items correlated significantly with accelerometer data [*r* = 0.40, *p* < .001, (31)]. A study using the German formulation of the items showed comparable values in terms of test retest reliability (*r* = 0.68, *p* < 0.05) and validity (*r* = 0.29 with accelerometer data, *p* < 0.05) (33).

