#### Data analysis

2.1.4

Data will be analyzed by the KIT research team. Questionnaire data are pseudonymized through personal codes and contact details are stored separately from questionnaire data. The identification of participants is possible only through a password-protected, locally stored file by the research team. A research assistant independently checks the accuracy of the data entry. Missing data will be analyzed to what extent they are systematic and, if necessary, treated with multiple imputation or the full-information maximum likelihood approach.

In order to ensure comprehensive analysis and interpretation of the data collected in our study, a multi-faceted statistical approach will be employed. Initially, repeated measures analyses of variance will be utilized to assess changes in subjective health, work ability, BMI, and physical activity behavior over time. This method is particularly effective for analyzing data where multiple measurements are recorded for the same subjects. Analysis of variance with repeated measurement allows for the evaluation of both within-subjects effects (changes over time) and between-subjects effects (differences among groups). In addition, latent growth curve modeling (LGCM) will be implemented to explore the trajectories of the aforementioned parameters across the study period. LGCM provides a flexible framework to model nonlinear growth trajectories, accommodating various shapes of developmental change (35). This is particularly pertinent for our study, as it enables the examination of individual differences in change patterns, thereby offering a deeper understanding of how rehabilitation programs impact individuals over time. Age, gender, the duration and the completement of the rehabilitation program will be included as control variables.

### Methods of Study Part 2

2.2

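### Six-month follow-ups after a 17-month recruitment window leave a limited seasonal component in adjacent physical activity contrasts and individual trajectories, and none of the listed controls can absorb it

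*Protocol article*

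**What the plan says.** Section 2.1.3 (Data collection) gives the calendar: "Data collection started in September 2023 and baseline measurements will be completed approximately in January 2025". It then fixes the spacing. "The interval between the measurement occasions after the rehabilitation is completed", that is t2 to t8, "is six months, resulting in a total follow-up period of three years". The pre and post "measurements are conducted at the beginning and at the end of the rehabilitation program to assess the effectivity". Section 2.1.2 adds "Typically, rehabilitation programs last three to four weeks", so t1 and t2 are less than a month apart.

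Physical activity (section 2.1.3.4) is the mean of two items, each counting active days in a week: "The first item refers to the last week and the second to a normal week". It is collected at every occasion, as is self-reported body weight.

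Section 2.1.4 plans repeated-measures analysis of variance and latent growth curve models. It notes that "LGCM provides a flexible framework to model nonlinear growth trajectories", and wants them for studying how patients differ in their course. It names a control set: "Age, gender, the duration and the completement of the rehabilitation program will be included as control variables". Season and calendar month are not mentioned.

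**The concern.** Three stated features combine. First, a six-month interval moves every participant to the opposite season at t3, t5 and t7 and back at t4, t6 and t8. Second, the recruitment window is not a whole number of years, so under even accrual the entry months are weighted towards autumn and winter and the seasonal swing does not fully cancel in the cohort mean. Third, the named controls describe the person or the programme. None of them moves with the season at each occasion.

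If activity is higher in summer, part of a rise from t2 to t3 and a fall from t3 to t4 could be season, yet be described as gain followed by relapse. At person level the swings of winter and summer entrants have opposite signs. A growth model with free or piecewise time scores could count that spread as differing response to rehabilitation. Durability is a stated aim of Study Part 1, so how six-month steps are interpreted matters.

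**Working it through.** The plan gives no figure for seasonality, so there is none to reproduce. The check derives the seasonal component from the plan's calendar.

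**Inputs from the article.** Accrual runs from September 2023 to about January 2025. Follow-ups are six months apart from t2 to t8. A programme lasts three to four weeks (0.85 month used for t1 to t2).

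**Assumptions, not in the article.** Accrual is even over the window. Season follows A·cos(2π(month − peak)/12), with the peak in mid-June, mid-July or mid-August. The summer-winter difference is D = 2A, between 0.2 and 0.5 SD.

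**1. Calendar.** September 2023 to January 2025 is 17 months. September to January occurs twice and February to August once. So 10 of 17 entry months (59%) fall in September to January, against 5 of 12 (42%) in a balanced year.

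**2. Cohort mean.** Let c be the seasonal cosine at a participant's t2 and c̄ its mean over the 17 entry months. Six months later the sign reverses, so the cohort change from t2 to t3 is −2A·c̄, which is |c̄| as a fraction of D.

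| Peak | c̄ at t2 | Change t2 to t3 | Share of D | For D = 0.2 to 0.5 SD |
|---|---|---|---|---|
| June | −0.219 | 0.44A | 22% | 0.04 to 0.11 SD |
| July | −0.181 | 0.36A | 18% | 0.04 to 0.09 SD |
| August | −0.095 | 0.19A | 9% | 0.02 to 0.05 SD |

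The mixed entry months thus cancel 78 to 91% of the swing. With accrual balanced over 12 months the cohort term is zero. Letting accrual ramp up or down fivefold hardly changes the July result (0.177A and 0.185A at t2 in absolute value, against 0.181A).

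**3. Between persons.** One person's seasonal change from t2 to t3 is −2A·c, with SD 2A·√(mean of c² − c̄²). For a June peak this is 2A·√(0.529 − 0.048) = 0.69 × 2A. July gives √(0.511 − 0.033) = 0.69 and August √(0.481 − 0.009) = 0.69. The SD is therefore about 69% of D: 0.69 × 0.2 = 0.14 SD to 0.69 × 0.5 = 0.35 SD.

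**4. What is not affected.** The seasonal terms at t2, t4, t6 and t8 are equal, so the 12-, 24- and 36-month contrasts carry none. The linear slope over seven equally spaced, alternating values is also zero. From t1 to t2 the cohort shift is −0.03A to −0.09A, about 1 to 5% of D.

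**5. Incomplete follow-up.** A person's slope is free of season only if the series ends at t4, t6 or t8. If it ends at t3, the slope per six months is −2c·A, with cohort mean 0.19A to 0.44A. If it ends at t5, it is −0.4c·A, with mean 0.04A to 0.09A. The article plans for 15% dropout after each occasion, so some series will end at t3 or t5.

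**The case against.** The strongest reply is that the main results survive. A reader might infer from the alternation that the durability or effectiveness results are biased. The documents do not support that. Same-season contrasts and the complete t2-t8 slope carry no seasonal term if retention does not depend on season of entry, and t1 and t2 are only weeks apart. This stands, and it limits the point to adjacent six-month steps and individual trajectories.

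The size also rests on an amplitude and a monthly accrual pattern that the article does not give. An adjacent-step artefact of 0.10 SD needs a summer-winter difference of 0.46 SD for a June peak (0.10/0.219), 0.55 SD for July (0.10/0.181) and 1.06 SD for August (0.10/0.0945). Only the first lies within the assumed range. The article's planning effect of 0.10 was derived from quality-of-life evidence and feeds an interaction across eight occasions, so it is a sense of scale rather than a benchmark for a t2-to-t3 change in activity.

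The item on a normal week may damp seasonality. At t2 the last-week item describes a programme week, which makes t2 to t3 hard to interpret anyway. A repeated alternation over seven occasions could also be noticed. These are fair points.

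For body weight, a reader might extend the argument, but the article offers nothing on its seasonal size or direction, so no claim is made.

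Finally, this is a condensed article, its analysis plan is not shown, and that plan could contain a season term. The growth model's form is not fixed either, so misattribution is possible, not certain. What remains is that the article does name a control set, and nothing in it can absorb season.

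**Conclusion.** The point holds in limited form. For physical activity, the stated calendar and spacing leave an alternating cohort component of about 9 to 22% of the summer-winter difference between adjacent occasions, or 0.02 to 0.11 SD if that difference is 0.2 to 0.5 SD. The larger effect is between persons: a spurious t2-to-t3 SD of about 69% of the difference, or 0.14 to 0.35 SD on the same range, which a flexible growth model can take for real differences in course. These figures rest on even accrual, a cosine season peaking in June to August and an assumed amplitude. The normal-week item could reduce them. The pre-post contrast is nearly unaffected, and the yearly contrasts and the complete-follow-up slope are unaffected under season-independent retention. The change is worthwhile because it is cheap and settles the reading of six-month steps before results are seen.

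**What to change.** In section 2.1.4, add season of questionnaire completion, for example the sine and cosine of calendar month, as a time-varying covariate in the growth model for physical activity, or in an equivalent mixed model. Entry months are spread over the year, so at any one occasion participants sit in different seasons and the term can be separated from time since rehabilitation. For BMI the same term can be an optional sensitivity analysis.

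When interpreting durability, report the same-season contrasts (t4, t6 and t8 against t2) alongside the full trajectory. There is no need to downgrade t3, t5 and t7.

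The cost is two extra model terms. No new data collection is needed, provided completion dates are recorded.
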